## Abstract

**Background:**

Physical activity (PA) is feasible, safe, beneficial, and recommended for pediatric patients with cancer. Nevertheless, PA levels remain low due to treatment-related effects (eg, fatigue, pain), isolation and immunosuppression, geographic and transportation barriers, and limited access to population-specific programming. Delivering PA by videoconference may address some of these barriers. Thus, IMplementation of Physical Activity for Children and adolescents on Treatment (IMPACT) was developed. IMPACT is an individualized, tailored PA intervention delivered by an exercise professional over videoconference and is being evaluated in a hybrid effectiveness-implementation trial.

**Objective:**

The objectives of this trial include (1) assessing the effectiveness of IMPACT on participants’ device-measured PA (primary effectiveness outcome) and secondary effectiveness outcomes, including participant- and caregiver-reported PA and participant- and caregiver-reported quality of life, symptoms, cognitive function, resource use, and participant physical fitness outcomes (ie, participants’ aerobic endurance, lower body flexibility, shoulder flexion range of motion, balance, functional mobility); and (2) assessing the implementation of IMPACT and the trial through evaluating recruitment, indices of feasibility, delivery time, expertise, cost, fidelity of intervention delivery, and adverse events.

**Methods:**

A single-arm, mixed-methods, type II hybrid effectiveness-implementation trial is being conducted, and the RE-AIM (reach, effectiveness, adoption, implementation, maintenance) framework is guiding evaluation. Pediatric patients with cancer and blood disorders diagnosed between 5 and 18 years of age are being recruited in Alberta. Following informed consent/assent and baseline assessments (ie, participants’ device-measured PA, participant- and caregiver-reported outcomes, participant physical fitness outcomes), participants receive individualized, tailored PA sessions up to 3 times/week for 15-45 minutes/session over 12 weeks from an exercise professional via videoconference. Assessments are then completed postintervention (with the addition of a participant and caregiver interview) and at 6- and 12-month follow-ups. With respect to RE-AIM, reach covers referral and participation rates, participants’ and caregivers’ personal and medical information, and the proportion of participants from rural versus urban locations. Effectiveness includes participants’ device-measured PA, participant- and caregiver-reported outcomes, and participant physical fitness outcomes. Adoption covers sources of referral. Implementation includes recruitment, feasibility, delivery time, expertise, cost, fidelity of intervention delivery, and adverse events. Maintenance includes participants’ and caregivers’ desire for ongoing access to PA, and participant- and caregiver-reported PA levels at 6- and 12-month follow-ups. Throughout the trial, quality improvement cycles occur every 6 months.

**Results:**

Funding was obtained in April 2022. Participant recruitment began in March 2022 and will conclude in December 2025. Interim analyses and additional analyses of selected trial data have been conducted, and publications are forthcoming. Full trial results will be analyzed and published following trial cessation.

**Conclusions:**

This work will provide insights into the effects of, and factors influencing, the implementation of an individualized, tailored PA intervention delivered by videoconference. Findings may support continued exploration of videoconference delivery as a strategy to ensure that more pediatric patients can access and benefit from PA.

**Trial Registration:**

ClinicalTrials.gov NCT04956133; https://clinicaltrials.gov/ct2/show/NCT04956133

**International Registered Report Identifier (IRRID):**

DERR1-10.2196/59302

## Introduction

### Background

Cancer among children and adolescents (ie, cancers diagnosed at <18 years) is relatively rare [1]. Recent estimates suggest that approximately 400,000 children and adolescents are diagnosed with cancer each year globally [2], representing <3% of all new cancer diagnoses annually [3]. Nearly 90% of children and adolescents diagnosed with cancer are anticipated to survive 5 or more years, and >70% will survive 10 or more years [4]. Despite this relatively positive prognosis, the disease remains a leading cause of morbidity and mortality among children and adolescents in North America [1,5], and is associated with negative effects in both the short term [6-8] and long term [9-14].

In the short term, children and adolescents on treatment for cancer (ie, pediatric patients with cancer) experience negative effects spanning physical (eg, pain, nausea [6]), psychological (eg, depression, anxiety [7]), social (eg, isolation [7]), and cognitive (eg, difficulty thinking and remembering [8]) domains of functioning. In the long term, children and adolescents living beyond treatment for cancer (ie, pediatric cancer survivors) may experience poorer physical (eg, decreased strength, increased fatigue [14]), psychological (eg, posttraumatic stress, fear of cancer reoccurrence [10,14]), social (eg, challenges in relationships with family and friends [10]), and cognitive (eg, reduced processing speed, impaired executive functioning, lower academic performance [9,15]) outcomes. This cohort is also at greater risk for secondary cancers, morbidity, and premature mortality [16-20]. Thus, identifying strategies to improve outcomes in both the short and long term is important.

Physical activity (PA; any bodily movement produced by skeletal muscles that requires energy expenditure [21]) may enhance physical, psychological, social, and cognitive domains of functioning among pediatric patients with cancer [22-24]. PA may reduce the severity of many of the negative effects experienced during treatment and enhance the overall quality of life among pediatric patients with cancer [25-27]. Indeed, systematic reviews have found that individualized, supervised PA during treatment—even during the intensive treatment phase—is safe and may improve a range of health outcomes [28,29]. Further, PA during treatment is associated with reductions in morbidity, secondary cancers, and premature mortality [30]. Recent reviews underscore the beneficial role of PA for pediatric patients with cancer [28,29,31,32], and guidelines and recommendation statements have been published suggesting that all pediatric patients with cancer *move more* [33].

Despite the documented benefits of PA and existing guidelines and recommendation statements [33], the desire and motivation of pediatric patients with cancer to engage in PA varies widely [34], and many stop engaging in PA during treatment [35,36] or take part in significantly less PA than their healthy peers [37]. This may be due to many of the barriers pediatric patients with cancer face when seeking to engage in PA, including adverse treatment-related side effects (eg, pain, nausea, fatigue), variable treatment timelines that differ significantly from child to child and include periods of isolation and immunosuppression [38,39], and the lack of pediatric cancer-specific PA opportunities (eg, interventions or programs) for this group [40]. Of the PA interventions and programs that are available, most are delivered at or near the hospital, which could pose an additional barrier to participation [41,42] and further disadvantage those who live in rural locations or farther from the hospital. Additionally, given that pediatric patients with cancer and their caregivers desire PA to be delivered close to or at home, the dominant focus on hospital-based delivery overlooks important preferences for PA within this population [41,42].

Exploring home-based PA delivery may be one way to address some of the barriers pediatric patients with cancer face when trying to engage in PA. However, relying solely on home-based PA programs may not successfully promote the adherence required to realize PA-related outcomes among this group [43]. Synchronous supervision of PA sessions by videoconference from exercise professionals may better support adherence to PA [40,43], ensure safe PA engagement, and reach more pediatric patients with cancer—a small and dispersed population [44]. Emerging evidence from recent trials suggests PA delivered by exercise professionals over videoconference is feasible and may improve physical outcomes (eg, physical fitness, flexibility, strength) among pediatric cancer survivors (ie, those off-treatment) [45,46]. This is bolstered by findings from videoconference-delivered (ie, telehealth) interventions focused on rehabilitation for pediatric patients with cancer and pediatric cancer survivors, which have found significant improvements in outcomes spanning PA limitations, participation restrictions, and quality of life [47,48]. In addition to being feasible and conferring benefits, videoconference delivery of PA may address another important interrupter to supervised in-person PA delivery—namely, circumstances such as cold and flu season or pandemics that limit access to pediatric patients with cancer (eg, ward closures) [45-48]. Finally, videoconference delivery of PA to this cohort could ensure that more pediatric patients with cancer have access to support from trained exercise professionals (eg, kinesiologists, clinical exercise physiologists, certified personal trainers), filling a gap within the Canadian context where exercise professionals (beyond physiotherapists and occupational therapists) are rarely, if ever, embedded within the pediatric cancer care system.

Indeed, in Alberta, there are no exercise professionals embedded within the pediatric cancer care system. However, there is support for providing PA in this cohort, positioning supervised videoconference PA delivery as a viable modality. Considering a desire to implement and evaluate a PA intervention with potential for sustainability and scalability in this context, a single-arm, type II hybrid effectiveness-implementation trial [49] is ideally suited to generate data assessing both the impacts of PA delivered by videoconference and the factors influencing implementation. This trial design has also been recommended by international experts to advance the field of pediatric exercise oncology [50]. Though videoconference delivery is a relatively novel approach, forgoing traditional feasibility and comparative designs is suitable given: (1) face validity for PA and its acceptability for pediatric patients with cancer [31,51]; (2) a growing evidence base from different, but related, populations (eg, young adults affected by cancer, adolescents with intellectual and developmental disabilities, adolescents with congenital heart disease) supporting the delivery of PA by videoconference [52-55]; (3) minimal risk associated with individualized, tailored PA for pediatric patients with cancer—with evidence to date supporting the safety of PA during this phase and of videoconference delivery (ie, few adverse events) [24,28,29,56]; and (4) rationale to gather more data on the effectiveness of PA interventions for pediatric patients with cancer [50] and on implementation metrics [47,48].

### Purpose and Study Objectives

The co-primary aims of this trial are to (1) assess the effectiveness of the videoconference-delivered PA intervention on participants’ device-measured PA (primary effectiveness outcome), as well as secondary effectiveness outcomes including participant- and caregiver-reported PA and participants’ quality of life, symptoms, cognitive function, resource use, and physical fitness outcomes (ie, aerobic endurance, lower body flexibility, shoulder flexion range of motion, balance, functional mobility); and (2) assess implementation of the PA intervention and the trial through evaluating recruitment, indices of feasibility, delivery time, expertise, cost, fidelity of intervention delivery, and adverse events.

## Methods

### Overview

This protocol paper was prepared following the SPIRIT (Standard Protocol Items: Recommendations for Interventional Trials) guidelines [57] and the TIDieR (Template for Intervention Description and Replication) checklist [58] (see Multimedia Appendix 1). The trial was registered with ClinicalTrials.gov [59] on July 09, 2021, and started at Stollery Children’s Hospital on March 1, 2022, and at Alberta Children’s Hospital on September 28, 2022 (see the “Ethical Considerations” section). This paper details the PA intervention and trial to enhance transparency in reporting and will serve as a reference for forthcoming papers. The CONSORT (Consolidated Standards of Reporting Trials) for eHealth interventions [60], the StaRI (Standard for Reporting Implementation Studies) statement [61], and the GRAMMS (Good Reporting of a Mixed Methods Study) checklist [62] will be followed when preparing and reporting the full trial results.

### Trial Design

A single-arm, mixed-methods, type II hybrid effectiveness-implementation trial is being conducted, and the RE-AIM (reach, effectiveness, adoption, implementation, maintenance [63,64]) framework is being used to guide evaluation. As above, a single-arm trial design was selected with consideration for the local Alberta context and the desire to develop and test an intervention that could be sustained and scaled into a routine care pathway. Mixed methods are being used to gather both qualitative and quantitative data to provide a more comprehensive understanding of the effectiveness and implementation of this novel mode of delivery. Quantitative and qualitative data are collected from participants, caregivers, and those involved in trial conduct (ie, health care providers, exercise professionals) at several time points, outlined in greater detail throughout the “Procedures” and “Data Collection” sections.

### Ethical Considerations

The research ethics application for this trial was submitted to the Health Research Ethics Board of Alberta (HREBA) on December 16, 2020, and approval was granted on February 16, 2021 (HREBA.CC-20-0364). Administrative approval was obtained from Stollery Children’s Hospital on February 12, 2021, and from Alberta Children’s Hospital on May 15, 2021. Due to delays related to the COVID-19 pandemic and hospital restrictions, recruitment opened at Stollery Children’s Hospital on March 1, 2022, and at Alberta Children’s Hospital on September 28, 2022. The first health care provider referral was received from Stollery Children’s Hospital on March 16, 2022, and from Alberta Children’s Hospital on October 19, 2022. Finally, research ethics board approval was granted by the Human Research Ethics Board at the University of the Fraser Valley on January 23, 2023 (approval number 101287). This approval was sought as the co-principal investigator (AW) moved institutions and onboarded additional local trial team members to support interview conduct and quality improvement cycle data collection.

In accordance with the principles of the Declaration of Helsinki and the ethics boards named above, all patients provide informed consent or assent to participate in this trial online via the web-based platform Research Electronic Capture (REDCap; Vanderbilt University) [65,66]. The designation of a Mature Minor, endorsed by Alberta Health Services, is being followed (ie, typically minors 14 years and older who can understand and appreciate the nature, risks, and consequences of participating in proposed procedures and are able to provide consent without the input of their legal guardian [67]). Caregivers also provide informed consent and, where indicated, provide consent on behalf of their child via REDCap. Health care providers and exercise professionals provide informed consent via REDCap to participate in semistructured interviews at regular intervals (see the “Quality Improvement Cycles” section).

Of note, all trial data are being deidentified and are accessible only to members of the trial team directly involved in trial conduct. Financial compensation is not provided to participants, caregivers, health care providers, or collaborators referring to the trial. Exercise professionals involved in PA sessions and assessment delivery are compensated for their time delivering PA sessions and conducting assessments of physical function, but do not receive compensation for completing interviews or data collection as part of the quality improvement cycles.

### Recruitment and Participants

Patients are recruited through referral from health care providers at Alberta Children’s Hospital or Stollery Children’s Hospital, via consent-to-contact forms, posters, self-referral documents, emails from the Kids Cancer Care Foundation (a local support organization), and word of mouth. Children and adolescents are eligible to participate if they (1) are between 5 and 18 years of age at enrollment; (2) have been diagnosed with any cancer or blood disorders; (3) are scheduled to receive, are currently receiving, or have completed treatment within the past 3 months; (4) are medically cleared to participate in PA; (5) have a caregiver (ie, an individual responsible for providing care to a child or adolescent diagnosed with cancer or a blood disorder) willing to complete assessments and be present during the PA sessions; and (6) are able to participate in English.

The decision to include pediatric patients with blood disorders was made considering that, in this Canadian context (ie, Alberta), pediatric patients with cancer and blood disorders are typically treated on the same unit/ward; the supervised, tailored, and low-risk nature of the PA delivered in IMplementation of Physical Activity for Children and adolescents on Treatment (IMPACT); early evidence suggesting the safety and benefits of PA in this cohort (ie, pediatric patients with blood disorders [68]); and consultations with clinical trial team members who supported, including pediatric patients with blood disorders.

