### Procedures

Following referral (health care provider or self-referral), a member of the trial team contacts the caregiver via their preferred method (ie, email, phone call, or text message) to describe the PA intervention and trial, ascertain interest, confirm eligibility, and share the link to the participant consent or assent, and caregiver consent forms via REDCap. Once consent (or assent, as appropriate) is provided by the patient (henceforth referred to as the participant) and caregiver, the participant is scheduled for a baseline (week 0) assessment, which includes the collection of the participant’s device-measured PA through a 7-day Fitbit (Google LLC) wear period and tracking log. Caregivers also complete a questionnaire covering personal and medical information, and participants and caregivers complete a series of questionnaires via REDCap assessing participant- and caregiver-reported PA as well as the participant’s quality of life, symptoms, cognition, and resource use. Participants additionally complete a physical assessment via videoconference, measuring aerobic endurance, lower body flexibility, shoulder flexion range of motion, balance, and functional mobility. Once baseline assessments are completed, participants are matched with an exercise professional and begin the 12-week, individualized, 1:1 PA intervention. Following the PA intervention, participants and caregivers complete the same assessments as at baseline (with the exception of personal and medical information, which is collected only at baseline) and are invited to complete a postintervention interview via videoconference. At 6- (week 24) and 12-month (week 52) follow-up time points, participants complete the same assessments as at baseline (week 0) and postintervention (week 12), with the exceptions of personal and medical information, which is collected only at baseline, and the interview, which is conducted only postintervention. To enhance data completeness, notifications of assessments are sent via REDCap, and reminders are sent every 3 days for up to 2 weeks if assessments are not completed at baseline, postintervention, and follow-up time points. See Figure 1 for the CONSORT diagram.

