### Data Collection

#### Assessment Timeline and Data Collection

As described above, assessments occur at baseline (week 0), postintervention (week 12), and 6- (week 24) and 12-month (week 52) follow-ups. See Table 1 for an overview of outcome measures and time points. Following the RE-AIM framework, multiple types of information are collected.

**Table 1 table1:** Outcome measures and time points.

Reach (throughout)	Effectiveness (weeks 0, 12, 24, and 52)	Adoption (throughout)	Implementation (throughout)	Maintenance (weeks 12, 24, and 52)
Referral rate (numbers and sources) Number of participants excluded and reasons for exclusion Participation rate (number of participants consenting to participate divided by the number of eligible individuals referred) Personal and medical information (ie, sex, gender, and other factors [eg, age, cancer diagnosis, sexual orientation, race/ethnicity, cultural background, and socioeconomic status]) of participating participants and caregivers (collected through caregiver-reported outcomes at baseline only) Proportion of participants from rural versus urban locations	Device-measured PA^a^ levels Participant and caregiver questionnaires (PA, quality of life, symptoms, cognitive outcomes, and resource use) Assessments of physical function (aerobic endurance, lower body flexibility, shoulder flexion range of motion, balance, and functional mobility) Interviews with participants and caregivers to explore the benefits of the PA intervention (at week 12 only) Resource use Direct and indirect costs (costs of intervention delivery and trial management)	Sources of referral Differences in referrals across referring sites	Trial retention Adherence to the PA intervention Percentage of missing data Interviews with participants and caregivers to explore their perceptions of feasibility (at week 12 only) Intervention delivery time and cost Trial delivery time and cost Expertise of exercise professionals PA session fidelity Adverse events (safety)	PA levels at 6- and 12-month follow-ups PA referral into community programs Access/use of maintenance offerings PA referral implementation

^a^PA: physical activity.

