#### Reach (Throughout)

Reach is assessed using data on referral rate (numbers and sources), number of participants excluded and reasons for exclusion, participation rate (number of participants consenting divided by the number of eligible individuals referred), personal and medical information (ie, sex, gender, and other factors such as age, cancer diagnosis, sexual orientation, race/ethnicity, cultural background, and socioeconomic status) of participating participants and caregivers, and the proportion of participants from rural versus urban locations. Where possible, information is also gathered from nonparticipating individuals via the consent-to-contact form and emails to assess reasons for trial refusal and to inform understanding of barriers to participating in the PA intervention and trial.

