### Data Analysis

Data will be analyzed and disseminated through conference presentations and manuscripts at multiple time points, including interim and trial cessation. To date, interim analyses have been conducted covering implementation metrics within the first 30 months, descriptive information, and individual changes in selected secondary outcomes pre- to postintervention [117]. No predetermined stopping rules were set within the context of the interim analyses.

At trial cessation, the full dataset will be analyzed. Single proportion inference tests and CIs will be used to determine the proportion of eligible participants who provided informed consent (or assent where appropriate) and adherence rates to the intervention components. Initial plans to analyze effectiveness data included generalized linear mixed models to examine changes over time in participants’ device-measured PA (primary effectiveness outcome) and in secondary effectiveness outcomes, multilevel modeling to examine site differences in relation to the primary and secondary outcomes, and inclusion and stratification of covariates (sex, gender, and other factors) to explore changes between cancer and blood disorder diagnoses and across age ranges (if sufficient power). Given the information presented in the “Sample Size” section, this trial is well below the sample size target. Thus, at trial cessation, alternative data analysis approaches will be considered. It is anticipated that the analysis will emphasize individual (idiographic) patterns and trajectories rather than relying solely on the more aggregated approach described above. Implementation data related to reach (referral rate, participation rate, participant personal and medical information, caregiver personal information, proportion of participants from rural vs urban locations), adoption (sources of referrals, differences in referrals across referring sites), implementation (trial retention, adherence to the PA intervention, percentage of missing data, intervention delivery time, expertise, PA session fidelity, trial delivery time, adverse events), and maintenance (participants’ and caregivers’ desire for ongoing access to the PA, participant- and caregiver-reported PA levels at follow-up time points) will be assessed using descriptive statistics via SPSS (IBM Corp) or R (R Foundation). The CONSORT diagram ([60]; Figure 1) will be completed to illustrate participant recruitment and retention in the trial.

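### The participation rate divides by eligible patients, but eligibility already requires a willing caregiver, so a caregiver's refusal can leave the denominator and push the rate up

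*Protocol article*

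**What the plan says.** - **Eligibility.** In the protocol article, *Recruitment and Participants*, the fifth criterion requires a caregiver who is "willing to complete assessments and be present during the PA sessions". The other criteria concern age, diagnosis, treatment window, medical clearance and English.
- **The rate.** Table 1 (*Assessment Timeline and Data Collection*) defines the participation rate as "number of participants consenting to participate divided by the number of eligible individuals referred". *Reach (Throughout)* gives the same ratio.
- **The inference.** *Data Analysis* plans single-proportion tests and confidence intervals to "determine the proportion of eligible participants who provided informed consent".
- **The contact.** Under *Procedures*, the team contacts the caregiver to describe the trial, then to "ascertain interest, confirm eligibility, and share the link" to the consent forms. Interest and eligibility are thus settled at the same stage, before consent. *Ethical Considerations* adds that caregivers give their own consent.
- **Other reach measures.** *Reach (Throughout)* also lists the referral rate and the "number of participants excluded and reasons for exclusion". Where possible, it gathers information from non-participants "to assess reasons for trial refusal and to inform understanding of barriers to participating in the PA intervention and trial". *Data Analysis* commits to completing a CONSORT diagram.
- **Progress.** *Results* reports 105 referrals, 42 scheduled calls and 26 consents. It gives no count of eligible patients and no count of exclusions by reason.

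**The concern.** A participation rate should show how many of those who could be offered the trial took it up. Most of the eligibility criteria can be judged without asking whether the family wants to take part. Caregiver willingness cannot: it is part of what consent expresses. Once it is a condition of eligibility, the same answer from the caregiver can remove a family from the denominator instead of counting against uptake.

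This differs from eligibility being unknown for families who were never reached. The circularity would remain even if every referred family were screened.

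Recruitment is named among the implementation outcomes of the second co-primary aim, and the intervention is meant to be sustained and scaled. *Limitations* foresees that the volume of assessments may burden caregivers as well as participants. If some caregivers decline for that reason, the participation rate is where a reader would expect it to show.

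**Working it through.** **Inputs.** All counts come from *Results*: 105 referred, 42 calls scheduled, 26 consents. The number otherwise eligible (D) and the number removed only because the caregiver is unwilling (k) are not given. Both are assumptions here.

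**Reproducing the stated figures.** 42/105 = 40.0% and 26/42 = 61.9%, as stated (40% and 62%). Neither is the participation rate as defined, because neither denominator is the eligible individuals referred.

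**Direction.** With C consents:

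- rate with caregiver refusals kept in: C/D
- rate with them removed: C/(D − k)
- ratio of the second to the first: D/(D − k), which is at least 1 for any k ≥ 0

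So the bias is zero at k = 0 and upward otherwise.

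**Illustration with D = 42.** This treats every scheduled call as otherwise eligible, which the article does not say. There are 42 − 26 = 16 non-consenting families.

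| k removed | Rate | Wilson 95% CI | Ratio |
|---|---|---|---|
| 0 | 26/42 = 61.9% | 46.8% to 75.0% | 1.00 |
| 2 | 26/40 = 65.0% | 49.5% to 77.9% | 1.05 |
| 4 | 26/38 = 68.4% | 52.5% to 80.9% | 1.11 |
| 8 | 26/34 = 76.5% | 60.0% to 87.6% | 1.24 |

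The exact (Clopper-Pearson) interval for 26/42 is 45.6% to 76.4%.

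**Illustration with D = 105.** This treats all referrals as otherwise eligible. There are 105 − 26 = 79 without consent.

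| k removed | Rate | Ratio |
|---|---|---|
| 0 | 26/105 = 24.8% | 1.00 |
| 8 | 26/97 = 26.8% | 1.08 |
| 20 | 26/85 = 30.6% | 1.24 |
| 40 | 26/65 = 40.0% | 1.62 |

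The interval is computed on whatever denominator remains, so it shifts with the coding choice and does not express uncertainty about it.

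**The case against.** The strongest reply is that nothing in the article says a declining caregiver is logged as ineligible. *Procedures* puts interest before eligibility, and *Reach (Throughout)* treats reasons for refusal separately from exclusions. A caregiver who says no when interest is ascertained could be recorded as a refusal among eligible patients, and then there is no bias. How a screening log separates the two is also the kind of detail an article may leave to the full protocol. This stands as far as the size goes: the number removed may be zero. It does not clear the definition, because the article itself fixes both the criterion and the denominator, and taken together they permit the circular reading.

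A second reply is that caregiver presence is required for sessions, so uptake among patients with a willing caregiver is a coherent quantity. That is fair, and it is a reason to report both rates. It does not remove the overlap between willingness as a criterion and consent as the outcome.

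A reader might go further and infer that reach as a whole is overstated, or that the plan hides caregiver unwillingness. The documents do not support either. Reach also includes the referral rate and exclusions with reasons, refusal reasons are sought where possible, and a CONSORT diagram is planned. Families removed from the denominator may stay visible there. *Limitations* speaks of assessment burden and does not name caregiver unwillingness as an observed barrier to recruitment.

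**Conclusion.** The point holds as a flaw in the definition of one rate. Taken literally, the fifth eligibility criterion and the eligible-only denominator let a caregiver's refusal count as ineligibility, and this can only raise the participation rate. The exclusion counts and the flow diagram may let a reader put such families back, provided caregiver unwillingness is recorded as its own reason. They do not correct the rate or its interval.

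The size is unknown. On the illustrative base of 42 calls, the rate moves from 62% to 68% with 4 families removed and to 76% with 8; it does not move if none is removed. It would be wrong to infer that the reported 62% is already inflated, since its denominator is scheduled calls and not eligible patients. Nor does anything support supposing that all 16 non-consenting families failed on this criterion alone.

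Severity is low. The article attaches no threshold or go/no-go rule to the participation rate, and the primary effectiveness outcome is unaffected.

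**What to change.** For the participation rate only, state that patients who meet every other criterion but whose caregiver is unwilling remain in the denominator and count as non-participants. Record caregiver unwillingness as a separate reason wherever contact records allow.

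Report three figures side by side:

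1. consents over patients eligible on the other criteria, with its confidence interval;
2. the rate as now defined;
3. consents over all referred.

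Enrolment eligibility does not change. The cost is one sentence of definition and a review of existing contact records. Some of those records may not allow re-coding, since contact can be by email or text as well as by phone, and the number that cannot be classified should be stated. The headline rate will be equal to or lower than the rate as now defined.
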